# Combined Acupoint Massage and Abdominal Mirabilite Application for Accelerating Gastrointestinal Recovery in Pediatric Patients After Endoscopic Retrograde Cholangiopancreatography: Protocol for a Randomized Controlled Trial

**DOI:** 10.2196/87961

**Published:** 2026-02-03

**Keywords:** acupoint massage, mirabilite, pediatric, endoscopic retrograde cholangiopancreatography, ERCP, gastrointestinal function, postoperative recovery, randomized controlled trial

## Abstract

**Background:**

Endoscopic retrograde cholangiopancreatography (ERCP) is crucial for managing pediatric hepatobiliary diseases but frequently results in postoperative gastrointestinal dysfunction such as delayed flatus and defecation, which can prolong recovery and increase the risk of complications. Nonpharmacological interventions such as acupoint massage and mirabilite application offer potential benefits, but evidence for their efficacy and synergy in children after ERCP is lacking.

**Objective:**

This study aims to evaluate the individual and combined effects of acupoint massage and abdominal mirabilite application on accelerating gastrointestinal recovery in pediatric patients following ERCP.

**Methods:**

A single-center, single-blind, randomized controlled trial will be conducted involving 72 children aged between 2 and 12 years who have undergone ERCP. Participants will be randomly allocated to 1 of the 4 groups: acupoint massage group (stimulating ST-36, ST-25, CV-12, and PC-6 for 2 minutes per point; twice daily), mirabilite group (abdominal application for 1 hour; twice daily), combination group (both interventions; at least 1 hour apart), or conventional care group. The primary outcome is the time to first postoperative flatus and defecation. The secondary outcomes include the frequency of postoperative nausea and vomiting and inflammatory markers. Data will be analyzed using intention-to-treat analysis with SPSS, using ANOVA, chi-square, and nonparametric tests as appropriate.

**Results:**

This trial is currently in progress, having received funding in January 2023 and July 2023. Participant recruitment commenced on November 1, 2024, with an anticipated completion date of October 30, 2026. As of January 2026, a total of 38 pediatric patients have been enrolled and randomized, while data collection and intervention delivery are ongoing. No interim analysis has been conducted. The final analysis will begin after recruitment and follow-up are complete, with primary results expected to be published in the second half of 2026.

**Conclusions:**

This study is the first to rigorously assess the efficacy and potential synergistic effects of acupoint massage and mirabilite application for enhancing gastrointestinal recovery after pediatric ERCP. Positive findings could establish a safe, nonpharmacological protocol to improve postoperative outcomes, reduce hospital stays, and minimize complications in this vulnerable population.

**Trial Registration:**

International Traditional Medicine Clinical Trial Registry ITMCTR2025000670; https://itmctr.ccebtcm.org.cn/mgt/project/view/3385640124071694411

**International Registered Report Identifier (IRRID):**

DERR1-10.2196/87961

## Introduction

### Background

Endoscopic retrograde cholangiopancreatography (ERCP) is a significant minimally invasive diagnostic and therapeutic procedure extensively used in the diagnosis and treatment of pediatric hepatobiliary disorders, including common bile duct stones, biliary strictures, biliary fistulas, and chronic pancreatitis [1-3]. Research indicates that children undergoing ERCP experience varying degrees of postoperative gastrointestinal dysfunction, including delayed passage of flatus and stool, abdominal distension, nausea, vomiting, and diminished bowel sounds [2,4]. If not promptly addressed, these complications may lead to severe outcomes, such as intestinal perforation and pancreatitis [5]. Postoperative gastrointestinal dysfunction not only increases the child’s discomfort but may also prolong hospital stays, raise intravenous nutrition requirements, and heighten the risk of complications, ultimately impacting the overall recovery process and exacerbating the economic burden on health care systems [6,7].

The mechanisms contributing to gastrointestinal dysfunction following ERCP are multifactorial, encompassing preoperative anxiety, opioid use, mechanical stimulation of the intestines from surgical procedures, vagal nerve dysfunction, and postoperative inflammatory responses [8-10]. Furthermore, the gastrointestinal development of children is incomplete, and their metabolic and neuroregulatory functions are more sensitive than those of adults, potentially exacerbating the delay in postoperative gastrointestinal recovery [11,12]. Current postoperative management strategies have shown limited effectiveness in the pediatric population. For instance, the administration of low-dose opioids after gastrointestinal surgery fails to alleviate postoperative pain and is associated with an increased incidence of postoperative gastrointestinal dysfunction [9]. Currently, there is no efficient, safe, and adherence-friendly specific protocol specifically designed to enhance gastrointestinal function in children after ERCP, highlighting the pressing need to explore nonpharmacological, low-risk alternative therapies.

Traditional Chinese medicine (TCM) posits that postoperative gastrointestinal dysfunction is categorized as “abdominal distension” or “constipation,” with the underlying pathogenesis frequently associated with Qi stagnation and bowel obstruction [13-15]. Acupoint massage stimulates specific acupoints to unblock meridians and harmonize Qi and blood, thereby enhancing gastrointestinal motility [16,17]. Research has demonstrated that massage activates parasympathetic nerve activity, promoting intestinal movement [18]. The topical application of mirabilite (sodium sulfate) aligns with TCM’s principle that “external treatment corresponds with internal treatment.” This substance possesses a cold nature and salty flavor, allowing it to clear heat, reduce swelling, and soften hardness to disperse masses; its high osmotic properties alleviate edema of the intestinal wall and stimulate local nerve reflexes, thus accelerating the recovery of bowel function [19]. The integration of these 2 methods creates a “comprehensive internal and external treatment” model; massage regulates the overall organ function and Qi, while mirabilite addresses localized swelling and constipation. This approach is advantageous due to its noninvasive nature, the ease of application, and cost-effectiveness, making it particularly suitable for pediatric patients who are intolerant to medication.

Research on adults has confirmed the effectiveness of the topical application of mirabilite in enhancing gastrointestinal function and reducing inflammation following laparoscopic cholecystectomy and laparoscopic appendectomy for mild acute biliary pancreatitis [20,21]. Additionally, acupoint massage has been shown to improve gastrointestinal function in patients undergoing gynecologic laparoscopic procedures and gastrointestinal surgery [17,18]. Despite the potential demonstrated by single therapies in adult studies, there is a significant lack of high-quality evidence supporting the use of acupoint massage in conjunction with the topical application of mirabilite to enhance gastrointestinal function in children following ERCP. Existing research not only lacks evidence for the effectiveness of acupoint massage, topical application of mirabilite, and their combined interventions for improving gastrointestinal function following ERCP in children but also fails to standardize intervention parameters related to gastrointestinal recovery in this population, such as the choice of acupoint for massage, duration of the procedure, and dosage of mirabilite. We hypothesize that all 3 intervention strategies will shorten the recovery time of gastrointestinal function and reduce postoperative adverse reactions compared to standard care, and the combined group is expected to yield the best results.

This protocol uses a 4-group parallel control design, comprising an acupoint massage group, a mirabilite external application group, a combined intervention group, and a routine care group. The primary objective is to compare the independent and synergistic effects of acupoint massage and mirabilite external application on the recovery of gastrointestinal function, specifically the time to first flatulence and defecation following pediatric ERCP. The secondary objective is to clarify the differences in the effects of various interventions on secondary outcomes, including the frequency of postoperative nausea and vomiting (PONV), as well as inflammatory markers, such as serum amylase and white blood cell (WBC) count. Additionally, the operational standards, including massage techniques, the duration of mirabilite application, and the evaluation processes of interventions, will be standardized to ensure methodological rigor, thereby providing a reliable basis for subsequent clinical translation.

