### Study Aims

This study aims to comprehensively evaluate the effects of acupoint massage, the external application of mirabilite, and their combined intervention on gastrointestinal function recovery in children following ERCP procedures. The primary objectives include comparing the efficacy of the 3 interventions—acupoint massage, mirabilite application, and the combined approach—against a routine care group, specifically in terms of shortening the time to first postoperative flatus and bowel movement. Additionally, this study aims to clarify whether the combined intervention offers advantages over individual therapies to determine the optimal clinical strategy. The secondary objectives involve assessing the degree of improvement in postoperative symptoms, including PONV; analyzing changes in inflammatory markers, including serum amylase and WBC count; and verifying the safety of the interventions regarding issues such as skin irritation and procedural tolerance. This research not only determine the optimal strategy to address the existing evidence gap in accelerated recovery following pediatric ERCP but also provides a scalable, standardized protocol for rapid postoperative recovery in pediatric patients.

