## Methods

### Study Design

A parallel 4-group, single-blind, randomized controlled trial (RCT) will be conducted from November 1, 2024, to October 30, 2026. The study will take place in the pediatric department of Shuguang Hospital in Shanghai. After baseline assessments, eligible participants will be randomly assigned in a 1:1:1:1 ratio to 4 groups: acupoint massage group, mirabilite group, combination group, and conventional care group (Figure 1; Table 1). Table 2 presents the content and procedures used in each intervention group. The standardized intervention manual can be found in Multimedia Appendix 1. The primary outcome measure will be the time to postoperative gas passage or stool, whereas the secondary outcomes will include the incidence of PONV as well as changes in inflammatory markers. This study will adhere to the SPIRIT (Standard Protocol Items: Recommendations for Interventional Trials) guidelines (Multimedia Appendix 2) [22]. This protocol was registered at the International Traditional Medicine Clinical Trial Registry (ITMCTR2025000670) on April 7, 2025.

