### Data Analysis

Statistical analyses will be performed using SPSS (version 25.0; IBM Corp) and RStudio (Posit PBC), incorporating the *survival* package. A 2-sided significance level of .05 will be applied for all tests, and an intention-to-treat analysis will be implemented to handle missing data.

Categorical baseline variables will be summarized as frequencies and percentages, with group comparisons conducted using chi-square tests or Fisher exact tests as appropriate. Continuous variables will be described as mean with SD if normally distributed and compared via 1-way ANOVA; nonnormally distributed variables will be presented as median with IQR and compared using the Kruskal-Wallis *H* test. Time-to-event analysis will be applied to the primary outcomes, namely time to first flatus and time to first defecation. Cumulative event rates will be visualized using Kaplan-Meier curves, and overall, between-group differences will be assessed via the log-rank test. To address multiple comparisons, a prespecified hierarchical contrast approach will be used. Primary contrasts, including each intervention group compared to the routine care group, will be evaluated using a Bonferroni-adjusted significance threshold of .0167. Exploratory pairwise contrasts between the combination group and each monotherapy group will be conducted only if significant differences are observed in the primary contrasts. Additionally, a Cox proportional hazards regression model will be used to estimate adjusted hazard ratios with 95% CIs for each intervention relative to routine care while controlling for baseline covariates identified in univariable analysis with a *P* value of <.10.

The secondary outcome analysis will include comparisons of PONV incidence using chi-square tests, with Bonferroni-adjusted pairwise testing where applicable. Inflammatory markers, including WBC count and serum amylase, will be analyzed using repeated-measures ANOVA to evaluate changes at 3 hours after surgery and on the morning of postoperative day 1. Safety outcomes will be summarized descriptively, and between-group differences in adverse events will be examined using chi-square or Fisher exact tests.

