The core innovation of this study is the introduction of a combined intervention model that uses acupoint massage to regulate organ Qi and enhance gastrointestinal motility, alongside the external application of mirabilite to alleviate swelling and promote bowel movements. This integrated approach aims to create a synergistic effect that comprehensively supports the recovery of gastrointestinal function.

This research uses a rigorous RCT design, systematically evaluating the effects of acupoint massage, external application of mirabilite, and their combined approach on the improvement of gastrointestinal function in children after ERCP, which clearly distinguishes the independent contributions of each intervention and their potential synergistic effects, thus providing a reliable basis for determining the optimal treatment strategy. Furthermore, this study aims to establish standardized operational parameters for acupoint massage and the external application of mirabilite for children, including acupoint selection, techniques, treatment frequency, and duration for external application, laying the groundwork for future clinical applications. The research pays attention to clinical end point and biological indicators, aiming to provide preliminary evidence on the mechanisms of action of the interventions, especially concerning their anti-inflammatory effects. Additionally, rigorously recorded safety data that meet expectations will become crucial for supporting clinical promotion. This study has significant advantages, as a noninvasive, nonpharmacological external treatment method; its high safety and ease of operation make it more acceptable to children and parents. Compared to mandatory early ambulation, this method is less painful, with low costs for mirabilite and controllable labor costs, providing good health economic value.

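### Synergy is part of the stated primary objective, but no planned analysis estimates it, and the combination-versus-monotherapy contrasts cannot tell synergy from additivity

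*Protocol article*

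**What the plan says.** The Background section states the objective as "The primary objective is to compare the independent and synergistic effects of acupoint massage and mirabilite external application", measured by time to first flatus and first defecation. Study Aims leads with each of the three interventions against routine care, then adds that "this study aims to clarify whether the combined intervention offers advantages over individual therapies". The Abstract's conclusions describe the trial this way: "This study is the first to rigorously assess the efficacy and potential synergistic effects of acupoint massage and mirabilite application". The Discussion names synergy as a target in its opening and closing paragraphs, and in between says that the design "clearly distinguishes the independent contributions of each intervention and their potential synergistic effects".

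The Data Analysis section fixes the analysis of both primary endpoints:
- Kaplan-Meier curves and an overall log-rank test;
- three primary contrasts, each intervention against routine care, at .0167;
- a Cox model giving adjusted hazard ratios for each intervention relative to routine care;
- a conditional step: "Exploratory pairwise contrasts between the combination group and each monotherapy group will be conducted only if significant differences are observed in the primary contrasts".

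No interaction, factorial or departure-from-additivity estimate is stated. Children are "randomly assigned in a 1:1:1:1 ratio to 4 groups": massage, mirabilite, both, or neither.

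**The concern.** The four arms form a complete 2x2 layout, so synergy has a definite meaning here: the interaction between the two therapies on a stated scale. The plan names synergy as a target but gives it no estimate. The only comparisons that set the combination against the single therapies ask whether it is better than each of them. If both therapies work and their effects simply add, the combination will usually be better than each, with no synergy at all.

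Two things are at stake. A ranking with the combination first could be read as evidence of synergy when it is what additivity predicts. And whether the comparison named in Study Aims is tested at all depends on a gate that the text leaves undefined.

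**Working it through.** **1. The plan's own sample size.** Inputs from the Sample Size section: one-way F test, four groups, f = 0.593, α = .05, power .95. With noncentrality N·f² and 3 and N−4 degrees of freedom, power is 0.946 at N = 52, 0.950 at N = 53 and 0.962 at N = 56. The smallest N with equal groups is therefore 56, as stated. Allowing for 20% dropout, 56/0.8 = 70, which rounds up to 72 for four equal groups. The figure reproduces, but it sizes only the overall test. Its source trial had three arms (both therapies, massage alone, mirabilite alone) and no routine-care arm, so it gives no information on a 2x2 interaction.

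**2. An additive reference case.** The documents give no interaction effect and no four-arm means, so this is an assumption. Let routine care, massage, mirabilite and combination have means 0, −d, −d and −2d in SD units. The interaction is −2d − (−d) − (−d) + 0 = 0. The SD of these four means is √(2d²/4) = d/√2. Setting it to 0.593 gives d = 0.593 × √2 = 0.839 SD, or 0.839 × 13.03 ≈ 10.9 hours with the protocol's SD.

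**3. What the planned contrasts show when there is no synergy.** Simulation of 100,000 trials with normal outcomes and pairwise t tests, at 18 per arm (72 randomized) and 14 per arm (56 evaluable):

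| Result | 18 per arm | 14 per arm |
|---|---|---|
| Combination has the best mean | 99% | 98% |
| Combination beats at least one monotherapy at .05 | 83% | 74% |
| Combination beats both at .05 | 54% | 41% |
| Interaction test significant at .05 | 5% | 5% |

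The ordering is nearly certain, and significance against both monotherapies common, although synergy is absent by construction. The interaction test rejects at its nominal rate.

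**4. The gate.** In the same simulation, if any one primary contrast significant at .0167 opens the gate, it opens in about 99% of trials at 18 per arm (97% at 14). If all three must be significant, it opens in about 34% (23% at 14). The text does not say which rule applies.

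**5. Precision of the interaction.** The standard error is √(4/n) SD: √(4/18) = 0.47 and √(4/14) = 0.53. A pairwise contrast has √(2/18) = 0.33 and √(2/14) = 0.38. Two-sided power at .05 (noncentral t, 4n−4 degrees of freedom):

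| True interaction | 18 per arm | 14 per arm |
|---|---|---|
| 0.5 SD | 18% | 15% |
| 0.84 SD | 42% | 34% |
| 1.0 SD | 55% | 45% |

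**6. The planned scale.** From the Cox model, the interaction is log HR(combination) − log HR(massage) − log HR(mirabilite). If every child has the event (a best case), its standard error is again about √(4/n). The 95% CI for the ratio of hazard ratios is then the estimate multiplied and divided by exp(1.96 × 0.471) ≈ 2.5 at 18 per arm, and by exp(1.96 × 0.535) ≈ 2.9 at 14. The ratio detectable with 80% power is exp(2.80 × 0.471) ≈ 3.7 and exp(2.80 × 0.535) ≈ 4.5 respectively.

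**The case against.** A reader might infer that synergy is the whole primary objective and that the trial cannot address it. The documents support neither. The objective covers independent as well as synergistic effects. Study Aims leads with the comparisons against routine care, and the three primary contrasts match those exactly. The stated hypothesis is that all three interventions beat standard care and the combination does best, which is an ordering and not super-additivity. The sentence on combination versus individual therapies follows separately, so its rank is ambiguous and its clash with exploratory status is weaker than it first looks. The Abstract and one Discussion paragraph speak of potential synergy, and elsewhere the Discussion states it as an aim; it is conjecture that the authors would claim synergy from a ranking.

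Nor does the planned model exclude the interaction. A Cox model with one indicator per active arm is the 2x2 model in another parametrization, and the interaction is a linear contrast of the same fit. What is missing is the prespecified contrast.

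The simulations use a continuous scale, whereas the planned analysis is log-rank and Cox, and additivity in hours is not additivity in log hazard. The percentages are therefore illustrative. Factorial main effects are also a matter of choice: they equal the effects against routine care only when there is no interaction.

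All of this stands and limits the point. It does not supply an estimate of synergy, and it does not support the Discussion's claim that the design clearly separates the two kinds of effect. Nor is this a detail left to an unseen analysis plan: the article itself fixes the contrasts, their hierarchy and the Cox comparisons.

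**Conclusion.** The point holds in limited form, as something that should be fixed. Synergy is named in the primary objective and repeated in the Abstract and Discussion, but no stated analysis estimates it. The contrasts planned for the combination cannot distinguish it from additivity: in the illustrative additive case the combination ranks first in 98% to 99% of trials and beats both monotherapies in 41% to 54%. The gate for these contrasts is undefined as to one or all. An interaction can be estimated from these arms, but imprecisely: power is 34% to 42% for 0.84 SD and 15% to 18% for 0.5 SD.

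The figures assume normal outcomes, equal components sized to give f = 0.593, and 14 to 18 children per arm. The conclusion about additivity does not depend on the exact percentages. It would be wrong to infer that the trial's confirmatory inference is compromised: the three contrasts against routine care at .0167 are unaffected.

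**What to change.** For each primary endpoint, prespecify the massage-by-mirabilite interaction from the planned Cox model, log HR(combination) − log HR(massage) − log HR(mirabilite), with its 95% CI. State that the scale is log hazard, label the estimate as low precision, and make it the only basis for any synergy statement.

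State which primary contrasts must be significant to open the gate. Report the combination-versus-monotherapy estimates with CIs whether or not the gated tests are run.

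Reword the Abstract's conclusions, the objective in the Background section, and the Discussion (opening, design and closing paragraphs) to say that synergy is explored with limited precision. The alternative is to remove synergy from the objective and conclusions. Factorial main effects may be added as supportive estimates but are not required.

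The cost is one contrast from a model already planned, a clarified gate and more modest wording. No new data are needed. The Results section reports 38 children randomized and no interim analysis, so the change can still be prespecified before any results are seen.
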